#### Inclusion criteria

The treating rehabilitation physician or his/her physician assistant will judge whether a potential participant meets the inclusion criteria. In order to be eligible to participate in this study, a participant must meet all of the following criteria:Diagnosis (suspected) of NAInitially, the (suspected) diagnosis of NA will be deduced from the information in the referral letter from the patient’s referring general physician or neurologist. If any uncertainty about the diagnosis remains, the rehabilitation physician or his/her physician assistant will contact the referring physician and/or patient. All patients will visit the specialised outpatient clinic, where the diagnosis will be either confirmed or discarded.NA predominantly present in the right upper extremityBeing in the subacute or chronic phase of NA (i.e. no inflammation of the plexus, in practice, > 8 weeks after attack onset)Presenting with scapular dyskinesiaAge ≥ 18 yearsRight-hand dominance (as indicated with an Edinburgh Handedness Inventory (EHI) score > + 40)Able to provide informed consent

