Neuralgic amyotrophy (NA) is a peripheral nervous system disorder in which (mal)adaptive central neuroplasticity might be important. There are several indications from clinical experience that (mal)adaptive central neuroplasticity is involved in this disorder [7]. However, little is currently known about the central mechanisms in this peripheral nervous system disorder. NA is a distinct peripheral nervous system disorder of the brachial plexus, with a yearly incidence ratio of 1/1000 [7, 8]. It can also be described as an asymmetric, autoimmune inflammation of the brachial plexus and peripheral nerves. In the acute phase, the inflammation causes damage to the affected nerves, leading to the characteristic acute severe upper extremity pain, multifocal paresis (i.e. muscle weakness) with functional impairments, and patchy areas of sensory loss. The long thoracic nerve that innervates the serratus anterior muscle, is affected in about 70% of patients with NA [9]. In a substantial subset of patients (> 50%), weakness of the serratus anterior muscle in the acute phase leads to compensatory, abnormal positioning and movement patterns of the scapula in the chronic phase. These patients develop chronic musculoskeletal pain in the paretic and compensating muscles, which leads to residual complaints of decreased functional capability of the affected upper extremity [10]. Many patients additionally suffer from impairment of activities of daily living, fatigue and decreased participation in daily occupations [7, 10]. The abnormal posture and movement patterns of the scapula are referred to as scapular dyskinesia. The concept of persisting shoulder complaints in NA is that through its plasticity, the motor system adapts to retain motor control of the shoulder region by forming compensatory movement patterns in the acute phase. After the acute phase, most of the damaged nerves recover over time and with this recovery, the strength of affected muscles, including the stabilising serratus anterior muscle, can return. However, recovery often does not lead to improved function because of dysfunctional coordination and instability of the scapula. Although some patients with NA recover well after 2–3 years, recovery is complicated in many [7, 9–12]. Residual complaints in NA are strongly correlated with persisting scapular dyskinesia [10]. There is currently no proven effective causative treatment for NA [13] and the usual care given, mostly standard physical therapy, is ineffective and may even worsen complaints in more than half of patients with NA [10]. The fact that scapular dyskinesia persists even when the peripheral nerves and strength of the stabilising scapula muscle recover implies that other, cerebral factors may play a role in explaining the residual symptoms and variable recovery in patients with NA. We introduce the concept that peripheral nerve damage in NA may lead to adaptations in motor planning and representations that are compensatory in the acute phase, but lead to impaired and dysfunctional motor control in the chronic phase (see Fig. 1).

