
#### Other parameters

Some measures will be collected to describe the study population and if applicable, to correct for possible confounding effects:A.Demographics: demographic data that will be collected includes age, sex and education levelB.NA characteristics: data on several characteristics of patients with NA will be collected. These include disease onset and duration, history of prior attacks and use of medication. Other characteristics may include, presence of atrophy, pattern of motor paresis, mechanical sensitivity of the plexus to pain, maximal severity of paresis during the attack and duration of primary pain.C.Comorbidity: relevant information on comorbid conditions and medication use will be collected.D.Motor imagery ability: there are individual differences in motor imagery ability [34]. As a subject’s ability to imagine movements might affect his/her performance on the motor imagery tasks in this study, motor imagery ability is assessed with the short version of the Kinesthetic and visual imagery questionnaire (KVIQ-10)*.* The KVIQ-10 assesses the clarity of the image (visual), and the intensity of the sensations (kinesthetic), that the subject is able to imagine from the first-person perspective [35].

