### Randomisation and blinding

Patients with NA will be randomly assigned to either the experimental intervention or to the usual care in a 1:1 ratio. Patients are randomized using a Good Clinical Practice (GCP)-compliant system (Castor Electronic Data Capture), which employs stratified, variable block randomisation. To prevent uneven distribution of certain characteristics across groups, randomisation will be stratified according to two factors: sex (male/female) and age (4 blocks: 18–30, 30–42, 42–54, > 54 years). Randomisation will be performed on site (at the Donders Institute for Brain Cognition and Behaviour, Centre for Cognitive Neuroimaging) after the participant has completed the baseline measurement (see Table 1).

Due to the project design, it is not possible to blind participants or the assessor. Participants will inevitably know whether they are receiving the rehabilitation programme or usual care. The assessor cannot be blinded either, for multiple reasons: all assessments are performed by a single assessor; as the number of assessments differs across groups, the assessor will know which participant belongs to which group; as the rehabilitation programme takes place at the assessor’s workplace facility, the assessor could be un-blinded on encountering a participant visiting the facility for treatment.

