### Statistics and data analysis

#### Proposed analysis

All continuous variables will be summarised as the number of (missing) observations, mean, standard deviation, median and range. Categorical variables will be summarised as the number of (missing) observations and number and percentage in each category. This will be done separately for each time point (baseline, outcome measurement(s) and follow up) and for the change from baseline for each intervention group.

The primary clinical outcome (SRQ-DLV score) and most other clinical outcomes are linear or quasi-linear. Group differences in the effects of the intervention on primary and secondary outcome measures and the influence of possible effect modifiers will be investigated using generalised estimated equations analysis. If necessary, analyses will be adjusted for group differences in functional capability of the upper extremity (SRQ-DLV score), age and sex at baseline. Data will be analysed according to the intention-to-treat principle. Data will be appropriately transformed if necessary, to satisfy modelling assumptions. Prior to locking of the data, a statistical analysis plan will be drawn up and approved by a statistician and the principal investigator.

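### Time since attack onset should be a fixed covariate in the primary SRQ-DLV model; the protocol leaves adjustment for it optional and data-dependent

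*Protocol article*

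**What the plan says.** **Entry.** The Inclusion criteria accept the subacute or chronic phase, defined as "in practice, > 8 weeks after attack onset". Neither the inclusion nor the exclusion criteria set an upper limit. Scapular dyskinesia must be present.

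**Natural history.** The Background states "After the acute phase, most of the damaged nerves recover over time" and that muscle strength can return with this, but that function often does not follow. It adds: "Although some patients with NA recover well after 2–3 years, recovery is complicated in many".

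**Randomisation.** Under Randomisation and blinding, "randomisation will be stratified according to two factors: sex (male/female) and age". Time since onset is not a factor.

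**Data collected.** Other parameters lists the disease characteristics: "These include disease onset and duration, history of prior attacks and use of medication". The section says that such variables serve to describe the population and, where relevant, to correct for confounding.

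**Adjustment.** The Proposed analysis reads: "If necessary, analyses will be adjusted for group differences in functional capability of the upper extremity (SRQ-DLV score), age and sex at baseline". It also provides for effect modifiers without naming any, and for a statistical analysis plan before data lock.

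**The concern.** A patient nine weeks after onset may still be regaining nerve function and strength. A patient several years out is less likely to be. If so, the two would be expected to change differently over the 18 weeks to the primary assessment, with or without the programme. Baseline SRQ-DLV measures current function and need not capture that difference in course.

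The adjustment rule leaves this variable out of its named set. It also makes adjustment depend on observed group differences, although a prognostic covariate improves precision whether or not the arms happen to differ on it. Other parameters keeps the option of using time since onset but makes it conditional too, so the two sections do not fix one covariate set. In an open-label trial with an unblinded assessor, a covariate chosen after looking at balance is open to question.

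At stake are the precision of the primary comparison and protection against a chance imbalance in a plausible prognostic factor.

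**Working it through.** The plan gives no figure on this point, so there is none to reproduce. The check sets a range.

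**Inputs**
- 25 patients per arm: 50 randomised 1:1.
- 42 patients required before dropout, power 0.90, two-sided 5%, standardised effect 0.29: from the sample size section. The 42 serves only as a yardstick here.
- ρ, the correlation of time since onset with 18-week SRQ-DLV change, given the other covariates in the model. The document gives none. **Assumed range: 0.1 to 0.5.**

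**Formulas**
- Share of residual variance removed by adjustment: ρ².
- Size of an adjusted trial equivalent to 42 unadjusted patients: 42 × (1 − ρ²), rounded up.
- Power of the adjusted test where the unadjusted test has 90%: Φ(3.24/√(1 − ρ²) − 1.96).
- SD of the chance difference between arms in a standardised covariate: √(2/25) = 0.283.
- Typical (one-SD) shift in the unadjusted estimate, in SDs of the outcome: ρ × 0.283. The 95% limit is 1.96 times this.

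| ρ (assumed) | Variance removed | 42 patients become | Power, from 90% | Typical shift (SD) | 95% limit (SD) |
|---|---|---|---|---|---|
| 0.1 | 1% | 42 | 90.3% | 0.03 | 0.06 |
| 0.2 | 4% | 41 | 91.1% | 0.06 | 0.11 |
| 0.3 | 9% | 39 | 92.5% | 0.08 | 0.17 |
| 0.4 | 16% | 36 | 94.3% | 0.11 | 0.22 |
| 0.5 | 25% | 32 | 96.3% | 0.14 | 0.28 |

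The probability that the arms differ by more than 0.5 SD in time since onset is 2 × (1 − Φ(0.5/0.283)) = 8%.

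**Price of the covariate.** Estimating one extra coefficient inflates the variance by a factor of about 1 + 1/(50 − 4) = 1.022. Net of this, ρ = 0.1 gives 0.99 × 1.022 = 1.012, a loss of about 1%. At ρ = 0.5 the factor is 0.75 × 1.022 = 0.77. Break-even is at ρ² ≈ 0.021, or ρ ≈ 0.15.

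**Type I error of the unadjusted test.** Under no effect, and given a covariate imbalance of k standard errors, the test statistic is about N(kρ, 1 − ρ²).
- k = 2: rejection rate 5.3% (ρ = 0.1), 6.4% (0.2), 8.1% (0.3), 13.4% (0.5).
- k = 0: 4.0% (ρ = 0.3), 2.4% (0.5).
- Averaged over all randomisations it is 5%. Imbalances of two standard errors or more occur in about 5% of randomisations.

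**Stratification.** Two sexes by four age bands is 8 strata, about 6 patients each (50/8). A two-level phase factor would make 16 strata, about 3 each (50/16).

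**The case against.** **Adjustment is already allowed.** Other parameters lets disease onset and duration be used against confounding, so it would be wrong to infer that the protocol rules this out. That stands. But the permission is conditional and is not carried into the Proposed analysis.

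**This belongs in the statistical analysis plan.** Final covariate lists often do, and an article need not give them in full. Here, however, the article states a specific rule with a named set and a condition, and the objection is to that rule. Naming effect modifiers can fairly be left to the later plan.

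**The natural history is less clear-cut.** A reader might infer that the disease as a whole resolves in two to three years. The Background says this of some patients only, says that function often fails to follow nerve recovery, and entry requires dyskinesia, which may select against easy recoverers. A reader might also picture many patients who are years past onset; the text only lacks an upper limit and gives no distribution of duration. Nor does it show that late patients are stable. These points stand and are why ρ may be small.

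**Spontaneous recovery does not bias the trial.** Both arms are concurrent and randomised, so recovery acts on both. The 8% to 13% rejection rates apply only to an unlucky randomisation at ρ = 0.3 to 0.5. They are not the trial's error rate. This stands in full.

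**Conclusion.** The point holds as one of precision and chance imbalance. Time since onset, which the protocol's own account ties to recovery, is missing from the named adjustment set, and any use of it is conditional. The primary estimate remains unbiased in expectation and the overall type I error is kept.

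The size is uncertain because it rests wholly on the assumed ρ. Over 0.1 to 0.5, adjustment removes 1% to 25% of residual variance and the typical chance shift at 25 per arm is 0.03 to 0.14 SD. At the top of the range the 95% limit, 0.28 SD, is close to the planned effect of 0.29. That comparison is valid only if 0.29 is a standardised mean difference, which the article does not make clear: read that way, the usual two-sample formula needs about 250 per arm, not 42 in all. That is a separate matter.

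The absence of time since onset from the stratification is not a defect to correct; 16 strata for 50 patients would be too thin to help.

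**What to change.** In the Proposed analysis, replace the conditional rule for the primary SRQ-DLV model with a fixed one: the model includes baseline SRQ-DLV, age, sex and time since attack onset at baseline (for example log-transformed), whatever the observed balance. Change Other parameters to match, so that both sections give one covariate set, and carry it into the statistical analysis plan before data lock. Leave the randomisation as it is. Examining phase as an effect modifier is optional and should be labelled exploratory.

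The cost is a sentence in each section and one degree of freedom for time since onset. The variable is already collected. If ρ is below about 0.15 the gain is nil or a loss of up to about 2% in variance; above that it grows at no cost in patients.

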#### Exclusion criteria

For the patients with NA, the treating rehabilitation physician or his/her physician assistant will judge whether a potential participant meets one or more of the exclusion criteria. A potential participant who meets any of the following criteria will be excluded:Prior NA attacks of the lumbosacral plexus or the left upper extremityPrevious participation in the specific rehabilitation programme offered at the Radboudumc or the rehabilitation centre KINOSOther neuromuscular disease affecting the shoulder girdleCentral nervous system disorder or neurological disorder (e.g. Parkinson disease, stroke etc.)Pre-existing (bio)mechanical constraints of the shoulder girdleA history of or recent periarticular fractures of the shoulderPast surgery of the shoulderDepressive mood disorder, as indicated by a score > 5 on the Beck Depression Inventory Fast Screen (BDI-FS)Severe comorbidityOngoing participation in another scientific study that might interfere with the current study

Exclusion criteria for undergoing MRI are:Pregnancy (current or planned within the study period)The presence of metal parts that cannot be removed, in or on the upper body (including plates, screws, aneurysm clips, metal splinters, piercings, medical plasters or ossicle prosthesis but with the exception of dental fillings or crowns)The presence of an electric implant (e.g. pacemaker, neurostimulator, insulin pump)History of brain surgeryClaustrophobiaEpilepsy

#### Participant selection and enrolment

Figure 3 provides a flow-chart of the recruitment, consent and other procedures of patients in the NA-CONTROL study.

**Fig. 3 Fig3:**
[figure not shown]
Flow-chart of patient recruitment, consent and other procedures of the study. NA, neuralgic amyotrophy

##### Identifying potential participants

All patients with NA that are newly referred to the Muscle Center of the Radboudumc during the study inclusion period will be checked for eligibility (i.e. meeting inclusion criteria 1–5) by a member of the treatment team through evaluation of the referral information. Eligible patients are informed about the NA-CONTROL study and their eligibility by post. At least a week after this notification letter is sent, a member of the treatment team will contact the patient to ask for his/her consent to be contacted by the coordinating researcher. Patients who express interest and provide consent will receive the extensive trial information package by e-mail.

##### Consenting participants

The coordinating researcher will contact patients who consent 7–14 days after the extensive trial information has been sent. After providing further clarification if needed, the coordinating researcher will state the inclusion and exclusion criteria. If the patient meets the inclusion and exclusion criteria, the researcher will ask the patient for oral consent and the baseline measurement will be scheduled.

Written informed consent will be obtained by the coordinating researcher at the research location. prior to the start of the baseline measurement. All participants will receive a copy of the signed informed consent form. The original signed informed consent forms will be kept at the study site. After written informed consent is obtained, the patient’s hand dominance will be determined using the Edinburgh handedness inventory (EHI) [15] and the patient will be screened for signs of depressive mood disorder using the Beck Depression Inventory-Fast Screen (see “Inclusion criteria”, “6” and “Exclusion criteria”, “8”, respectively).

Patients’ participation will be noted in their medical chart. As per national regulations, all participants’ general practitioners will be notified of their participation.

##### Ineligible and non-recruited patients

A patient’s decision to decline participation will in no way affect their treatment at the Radboudumc. This is clearly communicated to patients during all contacts. For patients who are not eligible, who express that they are not interested in participation or who do not meet all inclusion and exclusion criteria, the usual procedure is followed; they will be put on the regular waiting list for a consultation at our expert outpatient clinic. The content of the rehabilitation programme is the same for patients that participate in the trial as for those that receive the rehabilitation programme outside the study.

### Outcomes

See Table 1 for an overview of all outcome measures and their corresponding collection time points.

**Table 1 Tab1:**
[figure not shown]
Standard protocol items: recommendation for interventional trials (SPIRIT) figure: schedule of enrolment, intervention and assessments during the trial. t_5_ is only applicable for patients in the usual care group. Patients in the usual care group start with the rehabilitation programme after the outcome measurement at t_4_. For this group, t_1_, t_2_ and t_3_ take place after t_4_. Abbreviations: 3D: 3 dimensional; BDI-FS: Beck depression inventory – fast screen; CIS-fatigue: checklist individual strength – fatigue; COPM: Canadian occupational performance measure; DASH: disability of arm, should and hand; EHI: Edinburgh handedness inventory; HLJT: hand laterality judgment task; KVIQ-10: kinesthetic and visual imagery questionnaire-10; MPQ: McGill pain questionnaire; MRI: magnetic resonance imaging; NA: neuralgic amyotrophy; NENS: neuromotor encoding in neuromuscular scapular dyskinesia; PAM: patient activation measure; PSEQ: pain self-efficacy questionnaire; SAE: serious adverse event; SEPECSA: self-efficacy for performing energy conservation strategies assessment; SF-36: short-form 36; SRQ-DLV: shoulder rating questionnaire – Dutch language version; USER-P: Utrecht scale for evaluation of rehabilitation – participation

#### Primary outcome

##### Functional capability of the upper extremity

The primary outcome measure for the clinical part of the RCT is the change in SRQ-DLV score from baseline to post intervention. The SRQ-DLV is a reliable and validated questionnaire measuring functional capability of the shoulder, arm and hand [16] and has been shown to be sensitive to (changes in) functional capability of the shoulder in patients with NA [14].

#### Secondary outcomes

Secondary outcome measures are divided into clinical measures and measures related to motor planning (see below).

##### Clinical

The secondary clinical outcome measures cover multiple domains of the International Classification of Functioning, Disability and Health [17]:A.Activities and function: these will be assessed by administration of the following additional questionnaireDisability of Arm, Shoulder and Hand (DASH)The DASH questionnaire measures the functional capability of the affected upper extremity and has good clinimetric properties [18].B.Personal factors: fatigue, pain, self-efficacy and patient activation are assessed using the following questionnaires:Checklist individual strength - subscale fatigue (CIS-fatigue)The CIS-fatigue measures experienced fatigue [19].2.McGill Pain Questionnaire (MPQ)The MPQ measures the pain experienced. It assesses the nature, intensity, location, course and effect of the pain on daily life [20].3.Self-efficacy for performing energy conservation strategies assessment (SEPECSA)The SEPECSA assesses how the patients perceive their ability to apply energy conservation strategies to their daily lives [21].4.Pain self-efficacy questionnaire (PSEQ)The PSEQ assesses the confidence that people with ongoing pain have in performing activities while being in pain [22].5.Patient activation measure (PAM)Patient’s activation with regard to their health and disease is assessed using the PAM. The PAM measures knowledge, skills and confidence in managing one’s own health and/or disease [23].C.Participation: participation is assessed using the following measures:Utrecht scale for evaluation of rehabilitation-participation (USER-P)The USER-P is used to evaluate the effect of outpatient rehabilitation on participation [24].2.Canadian Occupational Performance Measure (COPM)The COPM is used to evaluate occupational performance and satisfaction with performance of the most important daily occupations identified as problematic by the patient. It thus assesses occupational participation [25]. The COPM is administered during the first and last sessions of the specific rehabilitation programme [14]. These assessments will serve as a pre-intervention and post-intervention comparison within patients with NA who underwent the experimental intervention.D.Body functions: within the body functions domain, we will assess the reachable workspace and several muscles/muscle groups3D-reachable workspaceReachable workspace is an objective measure of upper extremity impairment [26]. It is quantified by the relative 3D surface area representing the portion of the unit hemisphere that is covered by the hand movements made during a standardised movement protocol [26]. The movement protocol covers cardinal movements of the shoulder and is performed in front of the Microsoft Kinect sensor-based reachable workspace analysis system [26].2.The following strength measurements will be performed to determine maximal force exerted with several muscles/muscle groups on both sides (left and right upper extremity)The serratus anterior muscle measured using the MicroFET2®, digital manual muscle dynamometer, with the arm lifted to shoulder level, in the scapular plane whilei.Reaching with the arm extendedii.Reaching with a flexed arm (elbow at 90°).Rotation of the shoulder measured using the MicroFET2®, digital manual muscle dynamometer, with the arm at 0° anteflexion, elbow flexed at 90° and thumb pointing upwardsi.Endorotationii.Exorotation.Hand grip measured using the Jamar® Hydraulic Hand dynamometer, with the arm at 0° anteflexion, elbow flexed at 90° and straight wrist.Pinch grip measured using the Baseline® LiTE Hydraulic Pinch Gauge with the arm at 0° anteflexion and elbow flexed at 90°. The pinch gauge is held between the index finger (top) and thumb.Key grip measured with Baseline® LiTE Hydraulic Pinch Gauge, with the arm at 0° anteflexion, elbow flexed at 90°. The pinch gauge is held between the thumb (top) and index finger (bottom).E.Quality of life: quality of life will be assessed using the Short-Form 36 (SF-36)The SF-36 assesses experienced health and health-related quality of life [27].
